#### Experimental group

Apart from receiving a generic self-help smoking cessation booklet, subjects in the experimental group will receive a specifically designed risk communication leaflet from oncologists/ oncology nurses during the medical consultation. They will be warned the risk of continued smoking which can affect their cancer treatment and prognosis. This brief advice aims to increase the risk perceptions and normative beliefs of participants, hence affect their behavioral beliefs and subjective norms towards quitting. Furthermore, subjects will receive a patient-centered motivational intervention by an experienced nurse counsellor focusing on: (1) risk communication based on self-regulation model of illness for cancer patients; (2) the stage-matched smoking cessation intervention (Table 1). The risk communication component focuses on the relationship of smoking and cancer diagnosis, treatment and prognosis as a trigger to think about quitting. The components are modified from another study to help lung cancer patients quit smoking, with a self-reported quit rate of 24 % at 6 months [20]. The stage-matched smoking cessation intervention aims to (1) increase awareness on the needs to quit smoking; (2) motivate and increase confidence in ability to quit; (3) set a quit plan and boost their self-efficacy to resist smoking; and (4) discuss possible withdrawal symptoms and relapse prevention strategies. The counselling process will take about 15–30 min. In addition, each subject will receive at least one boost up telephone intervention within one week and another telephone intervention within one month by nurse counsellor. The follow up intervention aims to assess the progress of their action plan and barriers encountered in the behavioral change process as well as to engage them in the process, enhance their self-efficacy, and identify individual barriers and facilitators. Each telephone counselling will take 10–15 min.

**Table 1 Tab1:** Outline of smoking cessation intervention to be delivered by nurse counselor

At baseline
Stage-matched Smoking Cessation Counseling
(a) Pre-contemplation: Increase awareness of need to change; decisional balance; applying 5 “R”s: relevance, risks, rewards, roadblocks, repetition
(b) Contemplation: Motivate and increase confidence in ability to quit smoking; enhancing confidence in quitting by reinforcing achievement in previous quit attempt(s)
(c) Preparation: Set a quit plan and boost self-efficacy to resist smoking; discuss possible withdrawal symptoms and relapse prevention strategies
Risk communication via Self-regulation model of Illness
(a) Identity – recognizing the sign and symptoms of cancer
(b) Help patients understand the cause of cancer (smoking)
(c) Explain to patients the consequence of continue smoking or smoking cessation
(d) Emphasis the stage or cancer prognosis can be controlled by stopping smoking
(e) Reinforce patients’ abilities to change the overall timeline or prognosis of cancer if they can quit smoking substantially
At 1-week and 1-month telephone counseling
(1) Assess health-related lifestyle practices with emphasis on smoking cessation,
(2) Progress of patient’s action plan,
(3) Assess barriers encountered in the behavior change process,
(4) Boost self-efficacy, and
(5) Reinforce cancer related risk perceptions of continue smoking

### Measures

#### Structured questionnaire

A structured questionnaire will be developed by adopting or modifying international and/or locally validated instruments. The questionnaire gathers information including smoking and quitting history, risk perceptions of smoking [23], illness perception [24], intention to quit smoking (stage of readiness to quit) [21], antecedent factors of the TPB model (behavioral beliefs, outcome evaluations, normative beliefs, motivation to comply) [25], pros and cons of smoking (decisional balance), self-efficacy to resist smoking [26], quality of life (SF-12 v2) [27], other lifestyle risk factors (drinking, physical activities, and fruit and vegetable intake), demographic information such as age, gender, and marital status, and clinical information including height, body weight, body mass index, time to diagnose cancer, stage of cancer, number of tumor sites, blood pressure, and history of surgery, radiotherapy and chemotherapy. The demographic and clinical information will be obtained from the medical records.

### Process evaluation

Ten patients from the experimental group will be invited to participate in an in-depth interview after they have completed the 6-month follow up survey to examine their experience in quitting and the effect of the interventions from their perspective. Questions such as their satisfaction, perceptions on the advantages and disadvantages of the intervention, and any other suggestions for improvement will be explored and discussed

### Primary and secondary outcomes

The primary outcome is the self-reported 7-day point prevalence (PP) quit rate of the smoking cancer patients during 6-month follow up. The secondary outcomes include (a) self-reported 7-day PP quit rate at 12-month follow-up and the biochemically validated quit rate at 6-month follow-up (non-smoking status is confirmed by a carbon monoxide level in expired air < 9 ppm and saliva cotinine level < 115 ng/mL in parallel test), (b) percentage of patients reduced smoking by at least 50 % at 6- and 12-month follow-up compared to baseline, (c) percentage of patients with quit attempt(s) at 6- and 12-month follow-up, (d) change in the intention to quit smoking (stage of readiness to quit) at 6- and 12-month follow-up compared to baseline, (e) change in risk perceptions of continued smoking at 6- and 12-month follow-up compared to baseline, and (f) change in health-related quality of life at 6- and 12-month compared to baseline.

### Power calculation

Sample size is calculated by “Power Analysis and Sample Size (PASS) v. 13” (http://www.ncss.com/pass.html) and based on the main outcome variable according to the main hypothesis, the 7-day point prevalence self-reported quit rate at 6-month in the experimental group is higher than the control group. A previous RCT study [28] conducted in Australia, which applied motivational intervention to 137 smoking patients with mixed cancer sites. Based on that study, the self-reported 7-day point prevalence quit rate at 6-month follow up was 29 % for the intervention group and 18 % for the control group. To detect a statistical difference at 5 % significant level and a power of 0.8, 233 patients will be needed in each of the 2 groups (based on independent samples Fisher exact test). With reference to the local RCT on smoking cessation intervention for cardiac patients [22], we assume a 15 % attrition rate at the 6-month, and 274 patients will be required in each group to achieve a significant outcome. Accounting for the clustered randomized sampling design with 20 clusters (sessions) and an intra-class correlation of 0.002, 280 patients will be required per group, adding up the total sample size to 560 from the experimental and control groups together.

From the information provided by our clinical partners on site screening, there are around 2000 new patients per hospital per year. According to our previous qualitative study [23] conducted in an out-patient clinic on Chinese current smokers and ex-smokers, about 13.7 % patients continued smoking after receiving a cancer diagnosis (274: 13.7 % of 2,000). However, more than 50 % of these smokers were reluctant to quit (137: 50 % of 274). In a rough estimation, there will be around 700 eligible subjects in five acute Hospital Authority hospitals each year. We have confidence that we can recruit adequate subjects (560) according to the power analysis within an 18-month (78-week) recruitment period.

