### Analysis

Data analysis was performed using the Statistical Package for Social Science software, version 20.0 for Windows. When assessing the effectiveness of interventions between the two groups, we will first compare the baseline characteristics of the patients using chi-square test for categorical variables and *t*-test or Wilcoxon rank-sum test for continuous variables between the experimental and control groups. The primary analysis will be an unadjusted intention-to-treat analysis of the difference in self-reported 7-day point prevalence quit rate of the smoking cancer patients during 6-month follow up between the two groups. The analysis will be performed using Pearson’s chi-square test or with the use of Fisher’s exact test, if there were five or fewer participants per cell. Similar approach will be used to estimate the differences in secondary outcomes (e.g. self-reported 7-day PP quit rate at 12-month follow-up and the biochemically validated quit rate at 6-month follow-up, percentage of patients reduced smoking by at least 50 % at 6- and 12-month follow-up compared to baseline, and quality of life at 6 and 12 months) between groups. Crude odds ratios (ORs) for quitting will be estimated using logistic regression model and were compared with ORs that were adjusted for baseline variables (e.g. sex, age, education, stage of readiness). Those who are lost to follow-up or refuse to participate in the validation tests, will be treated as smokers with no reduction in cigarette consumption compared with (a) baseline, as the main analysis (by intention to treat), (b) the most recent level and (c) complete case (per protocol) analysis by excluding subjects with missing data as a sensitivity analysis.

For the process evaluation, all qualitative data from interviews will be tape-recorded and transcribed verbatim. Content analysis will be employed and themes identified. The constant comparative method will be used to search for common constructs and themes about the implementation and the effect of the intervention as perceived by the participating subjects.

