### Implications for clinical practice

This study will make an important contribution to evidence-based practice by testing the effectiveness of a tailored smoking cessation intervention targeting cancer patients.

If it is proven to be effective, the findings of this research have great potential to influence practice not just in out-patient clinics but also in wider health service and other public sector settings. Most importantly, the results primarily serve the purpose to support the development of clinical practice guidelines and interventions to promote smoking cessation in cancer patients to improve their cancer prognosis and in long-term, increase their survival time and quality of life. For the 280 cancer patients in the experimental group, we expect to help at least 81 to quit smoking at 6-month (29 %). For the sessions that are randomized as the experimental group, all cancer patients (no matter they participate or not into the study) would receive a specially designed leaflet and health warning from oncologists/ nurses. In addition, all the 580 subjects would receive a generic self-help booklet to help them quit smoking. Among the quitters who have lung cancer, their risk of cancer recurrence can be reduced by 20–47 %; the mortality rate (all-cause) can be reduced by 46–66 %; the risk of second primary tumor can be reduced by 76 % (among those with limited stage small cell lung cancer); and the likelihood of 5-year survival can be doubled, compared to still smokers [16]. Patients with cancer in other sites will also have clinical benefits after they quit smoking. Subsequently, the quality of life among cancer patients who stopped smoking can also be improved.

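### The 233 per group is a chi-square size labelled as Fisher exact, and the 15 % attrition uplift does not fit a main analysis that counts drop-outs as smokers, so the stated 80 % is not the power of the planned analysis

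*Protocol article*

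**What the plan says.** The Power calculation section of the protocol article takes six-month quit rates of "29 % for the intervention group and 18 % for the control group" from one earlier trial. The target is set as "To detect a statistical difference at 5 % significant level and a power of 0.8", without saying whether the test is one- or two-sided. The first result is "233 patients will be needed in each of the 2 groups (based on independent samples Fisher exact test". For attrition the section then says "we assume a 15 % attrition rate at the 6-month, and 274 patients will be required in each group". With 20 clusters and an intra-class correlation of 0.002, it ends at "280 patients will be required per group, adding up the total sample size to 560".

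The Analysis section makes Pearson's chi-square the primary test and reserves Fisher's exact test for cells of five or fewer. It counts patients lost to follow-up as smokers "as the main analysis (by intention to treat"), and leaves the complete-case analysis as a sensitivity analysis.

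The section Implications for clinical practice applies 29 % to all 280 patients in the experimental group: "we expect to help at least 81 to quit smoking at 6-month".

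**The concern.** Three statements about the same calculation do not fit together.

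- **The test.** The section on sample size names Fisher's exact test, and the section on analysis plans Pearson's chi-square. Only one of them can be the source of 233.
- **The attrition step.** Dividing by 0.85 replaces patients who will be missing from the denominator. Under the main analysis nobody is missing from the denominator: drop-outs stay in and count as failures. Attrition then lowers the rates, or is already contained in them, but it does not reduce the number analysed.
- **The expected yield.** The 81 quitters are 29 % of everyone randomised to the intervention. The attrition step treats 29 % as a rate among those followed up.

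This is the only justification of the sample size for the primary outcome. Depending on what 29 % and 18 % mean, the power of the planned analysis lies a little below 80 % or clearly above it. That affects how a null result would be read.

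**Working it through.** **Inputs.** From Power calculation: rates 0.29 and 0.18, alpha 0.05, power 0.80, attrition 15 %, 20 clusters, intra-class correlation 0.002, 280 per group. From Analysis: Pearson's chi-square, with drop-outs counted as smokers. Assumed: a two-sided test (this reproduces the plan's figure) and equal attrition in both arms.

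**1. The plan's 233.** The pooled, uncorrected formula is n = [z(0.975)·√(2p̄(1−p̄)) + z(0.80)·√(p1(1−p1) + p2(1−p2))]² / (p1−p2)², with p̄ = 0.235.

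- Numerator: (1.960 × 0.5996 + 0.8416 × 0.5946)² = 2.808
- Denominator: 0.11² = 0.0121
- n = 232.05, rounded up to 233

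So 233 is the chi-square size. Its power for that test is 80.2 % by formula and 80.5 % by exact enumeration of both binomials.

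**2. Is 233 a Fisher size?** Exact enumeration for Fisher's test gives:

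| n per group | Fisher, two-sided |
|---|---|
| 233 | 77.2 % |
| 247 | 79.8 % |
| 248 | 80.05 % |
| 250 | 80.3 % |

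A one-sided Fisher test does not give 233 either. It has 80.3 % power at 200 per group and 85.7 % at 233.

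**3. The plan's 274 and 280.** 233/0.85 = 274.1. With 233/20 = 11.65 patients per cluster, the design effect is 1 + 10.65 × 0.002 = 1.0213, and 274 × 1.0213 = 279.8, or 280. Both figures reproduce.

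**4. Which analysis this chain describes.** At 280 per group with design effect 1.026, and with 15 % removed from the analysis, the effective size is 280 × 0.85/1.026 = 232.0 per group. Chi-square power for 29 % against 18 % is then 80.0 %. The chain therefore describes the complete-case analysis, which the protocol lists as a sensitivity analysis.

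**5. Power of the main analysis at 280 per group.** The protocol does not say whether 20 clusters is per arm or in total. Three cluster sizes cover the range: 11.2 patients (560 over 50 sessions, being 10 at each of five sites), 14 (280/20) and 28 (560/20). The design effects are 1.020, 1.026 and 1.054.

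*Reading A: 29 % and 18 % are rates among patients followed up.* The analysed rates are 0.85 × 29 % = 24.65 % and 0.85 × 18 % = 15.3 %.

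*Reading B: 29 % and 18 % already count drop-outs as smokers.* The analysed rates stay at 29 % and 18 %.

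| Design effect | Reading A | Reading B |
|---|---|---|
| none | 79.2 % | 86.8 % |
| 1.020 | 78.4 % | 86.2 % |
| 1.026 | 78.1 % | 86.0 % |
| 1.054 | 77.0 % | 85.1 % |

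Under Reading A, 80 % before clustering would take 286 per group.

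**6. Expected quitters among the 280.** Reading B: 0.29 × 280 = 81.2, the protocol's figure. Reading A: 0.29 × 0.85 × 280 = 69.0.

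**The case against.** The strongest reply is that the planned analysis loses nothing that matters. The primary test is Pearson's chi-square, and 233 is right for it. Even with the lower rates, the smallest expected cell is 0.153 × 280 = 43, so Fisher's test will not be triggered. A reader might infer from the Fisher label that the trial has only 77 % power, or that it needs 248/0.85 × 1.02 = 298 per group (596 in total) instead of 560. The documents do not support that, because those figures belong to a test the trial will not run. This part of the reply stands in full.

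The reply continues that the attrition loss depends on an earlier trial that cannot be seen here. The only internal evidence, 81 of 280, treats 29 % as a rate among all randomised, which puts power above 80 %. Even on the other reading the loss is 1 to 3 points, small beside the uncertainty of rates taken from one study of 137 patients. This also stands as a statement about size. It rules out saying flatly that the trial falls short of 80 %, or that the expected number of quitters is 69.

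It does not rescue the text. The 81 quitters need Reading B, and the division by 0.85 needs drop-outs to be excluded. The protocol uses both, and the main analysis is consistent with the uplift on neither reading.

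**Conclusion.** The point holds as a fault in the stated basis of the sample size. It does not show that the trial is underpowered.

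- The Fisher label is wrong. The figure is a chi-square size, and the error has no effect on the power of the planned test.
- The attrition step does not match the main analysis. Power at 280 per group after clustering is about 77–78 % if 29 % and 18 % are rates among those followed up, and about 85–86 % if they already count drop-outs as smokers. The two readings lie about 8 points apart, and the protocol does not say which applies.
- The 81 expected quitters are right on the second reading and would be about 69 on the first.

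These results assume a two-sided test, equal 15 % attrition in both arms, the stated intra-class correlation of 0.002, and 11 to 28 patients per cluster.

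**What to change.** Keep 280 per group and change the text only:

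1. Give Pearson's chi-square test, two-sided, as the basis of 233 per group.
2. State whether the assumed 29 % and 18 % are rates among patients followed up or already count drop-outs as smokers.
3. Replace the division by 0.85 with the power of the main analysis at 280 per group. For rates among those followed up: expected rates 24.65 % and 15.3 %, power about 77–78 % after the design effect. For rates that already count drop-outs as smokers: no uplift, power about 85–86 %.
4. Make the expected number of quitters in Implications for clinical practice agree with that choice: about 69 on the first reading, 81 on the second.

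The cost is rewording. No patients are added, and neither the design nor the analysis changes. On the first reading the stated power becomes 2 to 3 points less favourable; on the second it rises by 5 to 6 points.

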### Randomisation

Randomization will be done with each session in an out-patient clinic as a cluster unit. Currently there are 10 sessions per week per study site. Before the study, we will randomly draw the sessions by computer generated random sequence (block randomization with each hospital as a block unit), so that 5 sessions will be treated as intervention group and another 5 sessions will be treated as control group per week. Participants who consent to participate in the study will be assigned to either intervention or control group depending on the out-patient clinic session that they are seeking consultation. By using this experimental design, we can ensure similar proportion of smoking cancer patients will fall into the intervention and control group in each out-patient clinic, and each out-patient clinic will have a similar proportion of cancer patients into the intervention/ control group. We expect the intervention and control group would have similar socio-demographic profile, smoking history, and clinical history and we shall check for any differences, and if any, we shall adjust for them in the analyses. In using the cluster randomization design with a session being a cluster unit, the patients who are randomized into the experimental and control groups would have less chance to meet each other in the out-patient clinic and discuss the contents of the smoking cessation interventions.

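### The power calculation uses 20 clusters where the randomisation gives 50 session slots; the input needs restating, but 280 per group stands unless 20 means the total over both arms

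*Protocol article*

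**What the plan says.** The Power calculation section works in three steps: 233 per group for the comparison of quit rates, 274 after 15% attrition, then the cluster step: "Accounting for the clustered randomized sampling design with 20 clusters (sessions) and an intra-class correlation of 0.002, 280 patients will be required per group". The total is 560.

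The Randomisation section makes the clinic session the cluster unit and gives the count per site: "Currently there are 10 sessions per week per study site". At each site "5 sessions will be treated as intervention group and another 5 sessions will be treated as control group per week". The opening of Methods/Design names five acute hospitals as the settings, and Procedure refers to five out-patient clinics.

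Under Implications for clinical practice, the text gives 280 patients in the experimental group and shortly afterwards says that "all the 580 subjects would receive a generic self-help booklet".

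**The concern.** Five sites with 10 weekly sessions each make 50 slots, 25 per arm. The power calculation uses 20 and calls them sessions, so it refers to the same unit. This is a disagreement between two stated figures, not a detail lost in condensing the protocol into an article.

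The number of clusters fixes the average cluster size and so the design effect. It also fixes the information available to a cluster-aware analysis. Ignoring the hospital blocks, 20, 40 or 50 clusters leave 18, 38 or 48 between-cluster degrees of freedom (clusters minus 2). If the count is wrong, the sample size could be wrong too, so the check is whether 280 survives the correct count.

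**Working it through.** **Inputs.** Quit rates: "was 29 % for the intervention group and 18 % for the control group". Error rates: "5 % significant level and a power of 0.8"; sidedness is not stated, and two-sided is assumed because it reproduces the plan's figure. Attrition 15%, intra-class correlation (ICC) 0.002 and 20 clusters come from Power calculation. Sessions per site and the 5:5 split come from Randomisation, and the five sites from Methods/Design.

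**Step 1, the plan's 233.** Two-proportion formula with pooled variance under the null and no continuity correction; mean proportion (0.29 + 0.18)/2 = 0.235:

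n = [1.960 × √(2 × 0.235 × 0.765) + 0.842 × √(0.29 × 0.71 + 0.18 × 0.82)]² / 0.11² ≈ 232.1, rounded up to 233. Reproduced. (The plan names Fisher's exact test as the basis. That is a separate matter; 233 is taken as given here.)

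**Step 2, attrition.** 233 / 0.85 = 274.1, given as 274. Reproduced.

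**Step 3, clusters.** Design effect DE = 1 + (m − 1) × 0.002, where m is patients per group divided by clusters per group. The text lists attrition before clustering, but the design effect can also be applied to the 233 evaluable patients and the result divided by 0.85. Both orders are shown.

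| Reading | Clusters per group | Attrition first | Clustering first |
|---|---|---|---|
| 20 in total | 10 | m = 27.4, DE = 1.0528, 274 × DE = 288.5 → 289 | m = 23.3, DE = 1.0446, 233 × DE / 0.85 = 286.3 (288 if rounded up at each step) |
| 20 per group | 20 | m = 13.7, DE = 1.0254, 274 × DE = 281.0 → 281 | m = 11.65, DE = 1.0213, 233 × DE / 0.85 = 279.96 → 280 |
| 50 slots of the design | 25 | m = 10.96, DE = 1.0199, 274 × DE = 279.5 → 280 | m = 9.32, DE = 1.0166, 233 × DE / 0.85 = 278.7 → 279 |

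Working backwards, 280/274 = 1.0219. This implies m = 1 + 0.0219/0.002 ≈ 11.9 and about 274/11.9 ≈ 23 clusters per group, which lies between the second and third rows.

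**Step 4, fit to the design.** At 10 sessions per site, 20 clusters in total is 20/10 = 2 sites; 20 per group is 40/10 = 4 sites. The plan has 5. If sessions are redrawn every week of the 78-week recruitment period, there are 50 × 78 = 3,900 session occasions, or 1,950 per arm. Then m = 274/1,950 ≈ 0.14, clusters are nearly all single patients, and DE is about 1. No reading of the randomisation yields 20.

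**Step 5, power at the planned size.** 280 × 0.85 = 238 evaluable per group, each divided by its design effect:

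- 10 clusters per group: DE = 1.0456, power 79.2%
- 20 per group: DE = 1.0218, power 80.2%
- 25 per group: DE = 1.0170, power 80.3%

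**The case against.** The best defence is that the plan's arithmetic can be reproduced. The other sample sizes in the calculation (233, 274, 280) are per group, so reading 20 as per group is natural. With clustering applied before attrition, that reading gives 279.96, which is 280. The 50 slots also give 280. At the stated ICC, no reading costs more than about one percentage point of power, and weekly redrawing would make 560 slightly generous. All of this stands. It shows that the sample size is not in error; it does not make 20 agree with five sites of 10 sessions.

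A reader might infer several stronger things that the document does not support:

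- **That the right answer is 289, not 280.** This needs 20 to be the total over both arms and the design effect to be applied after attrition. The text does not settle the first, and the other order gives 286 to 288.
- **That the 580 in the Discussion is a trace of a 578 (2 × 289) calculation.** Nothing in the text links them. Procedure and Power calculation both say 560, and the same Discussion section has 280 in the experimental group.
- **That the ICC is faulty because no source is given.** A condensed article may leave that justification to the full protocol.
- **That the trial is underpowered at larger ICCs.** With 50 slots and 238 evaluable per group, power would be 0.78, 0.75 and 0.66 at ICCs of 0.01, 0.02 and 0.05. Those values are assumptions of this review and appear nowhere in the plan, so they show sensitivity, not an error.

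**Conclusion.** The concern holds as a consistency error in a stated input. Twenty clusters, read either way, does not match the 50 session slots implied by Randomisation and Methods/Design, and the text leaves total versus per group open. The consequence for the sample size is small. With 20 per group or with the design's 50 slots, the requirement is about 279 to 281 and 280 stands. Only if 20 is the total does the requirement rise to about 286 to 289 per group, with power at 280 of about 79%.

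These figures rest on the plan's ICC of 0.002, equal cluster sizes, a two-sided test and 15% attrition. The 50-slot figure also assumes that each slot keeps its allocation throughout recruitment. Randomisation says that the draw is made before the study but describes the split per week, so this is not certain. The document does not support concluding that 560 is too small.

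**What to change.** In Power calculation, replace the 20 with the number of clusters the randomisation produces, in total and per arm. If slot allocation is fixed for the whole recruitment period, that is 50 slots, 25 per arm, about 560/50 ≈ 11 patients per slot, design effect about 1.02 at ICC 0.002, and 280 per group. If sessions are redrawn weekly, state that and give the resulting count. Randomisation should say which applies.

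Use the same session unit as the cluster in the analysis. The Analysis section names chi-square, Fisher and logistic regression methods without a cluster term, so this part needs a sentence there and is more than a change of wording.

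Correct 580 to 560 under Implications for clinical practice. A short table of power at larger assumed ICCs would be a useful but optional sensitivity check.

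The cost is a few sentences of text. The sample size stays at 560 and recruitment is unaffected.
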